### Definition of end of trial

The end of trial will occur once the primary outcome data has been collected for all patients and the one month follow-up notes review of the final participant has been performed.

### Discontinuation and withdrawal of participants from study treatment

Each participant has the right to withdraw from the study at any time. In addition, the investigator may discontinue a participant’s involvement in the study at any time if the investigator considers it would be harmful to keep a participant in the study. The reason for withdrawal will be recorded in the CRF.

If the participant is withdrawn due to an adverse event, the investigator will arrange for follow-up visits or telephone calls until the adverse event has resolved or stabilized, or until the end of the study when participant care will return solely to the GP. The participant’s data will be retained in the trial for the purpose of intention-to-treat analysis unless consent to do so is specifically withdrawn. This is in order to safeguard the validity of the data set. If a participant is found to be ineligible after they have been randomized then they will be removed from the trial. Their data will also be removed from the intention-to-treat analysis.

### Source data

Source documents are original documents, data and records from which participants’ CRF data are obtained. These include, but are not limited to, general practice medical records (from which medical history and previous and concurrent medication may be summarized into the CRF, as well as follow-up data at one month). CRF entries will be considered source data if the CRF is the site of the original recording (there is no other written or electronic record of data). In this study the CRF is being used as the source document for the documentation of inclusion and exclusion criteria, and baseline assessment information. Symptom diaries and telephone calls recorded onto CRFs are considered source data. All documents are stored safely in confidential conditions. On all study-specific documents other than the signed consent the participant will only be referred to by their study participant ID.

### Treatment medication

#### Description of study treatment

The study treatment is a single 10 mg dose of dexamethasone taken orally. The dose takes the form of five 2 mg dexamethasone tablets over-encapsulated into a single capsule and an over-encapsulated placebo identical in size, colour and taste. The drug acquisition, over-encapsulation, packaging and labelling was performed by Nottingham University Hospitals NHS Trust.

The labelling of medication packs conforms to Annexe 13 (GMP) and Article 13.3 of European Commission Directive 2001/20/EC. A template label was approved by the clinical trial team and provided to the manufacturer by the Chief Investigator. Each medication pack label is printed with a unique medication ID number to ensure dexamethasone and placebo medicine packs are indistinguishable and thus maintain allocation concealment. This randomized medication ID forms the identifier on the open code-break document sent with each delivery of medication packs to the University of Oxford PC-CTU. The medicines were received from the manufacturer and are stored securely by the clinical trials unit.

The trial centers are responsible for supplying the medication packs to the GP practices in their area, four to six packs at any one time, so that clinicians can draw from their allocation as recruitment proceeds. Trial centers keep a log of medication packs sent to a GP practice, with all medication packs signed for on receipt at the GP practice. Sites liaise with their local centre when more packs are required, and the local centre then liaises with the Oxford centre to send a further block to the local centre. At all times the medicines will be stored at room temperature, in line with the summary of product characteristics, SmPC. The study drug and placebo can be stored below 25°C and out of direct sunlight and are kept securely in the Oxford PC-CTU and on site, with controlled access by site trial staff. A formal risk assessment considering all the potential risks involved in the distribution of the trial medication will be written alongside a standard operating procedure detailing the exact procedure for the handling of all trial medication to ensure that any associated risks will be minimized.

#### Compliance with study treatment

The participant is observed taking the single dose of study medication once they have provided full informed consent.

#### Accountability of the study treatment

The study medication is supplied by Nottingham University Hospitals NHS Trust to the clinical trials unit. All movements of study medication between Nottingham University Hospitals NHS Trust and clinical trials unit are documented. The clinical trials unit will supply the allocated drugs to the local centers who distributed these out to the sites in their area. The clinical trials unit will keep logs of all medication IDs and where each drug is sent to, local centers will keep logs of all drugs allocated to them and the GP practices will keep local drug accountability logs, including drug allocation logs.

In the event that medication needs to be redistributed, a drug redistribution log must be completed to document the unique medication ID and must include a minimum of one release signature (origin site staff), one transporter signature (PC-CTU staff) and one receiving signature (new site staff), with approval from the MHRA.

Site-specific procedures will be followed in relation to disposing of and arranging for destruction of expired trial medication. Standard GP site procedures should be followed and the drug destruction log should be completed with the following details: date, unique medication ID, expiry date, quantity to be destroyed (number of tablets) and staff initials to confirm destruction.

#### Concomitant medication

Throughout the study the responsible clinician may prescribe any concomitant medications or treatments deemed necessary to provide adequate supportive care except for those listed in the exclusion criteria. If these are required, the participant will stay in the trial for purposes of intention-to-treat analysis. Any medication taken during the study other than the study medication will be recorded in the symptom diary or noted on notes review.

#### Post-trial treatment

Following the single dose of oral dexamethasone participants continue normal medical care by their GP.

### Safety reporting

#### Definitions

An adverse event (AE) or adverse experience is any untoward medical occurrence in a patient or any abnormal result from a clinical investigation in participants who have been administered a medicinal product,which does not necessarily have to have a causal relationship with this treatment (the study medication). An AE can therefore be any unfavorable and unintended sign (including an abnormal laboratory finding), symptom or disease temporally associated with the use of the study medication, whether or not considered to be related to the study medication. An adverse reaction (AR) will be defined as all untoward and unintended responses to a medicinal product related to any dose. The phrase ‘responses to a medicinal product’ means that a causal relationship between a study medication and an AE is at least a reasonable possibility - the relationship cannot be ruled out. All cases judged by either the reporting medically qualified professional or the Sponsor as having a reasonable suspected causal relationship to the study medication qualify as adverse reactions. A serious adverse event (SAE) will be defined as any untoward medical occurrence that at any dose results in death, is life-threatening, requires inpatient hospitalization or prolongation of existing hospitalization, results in persistent or significant disability and/or incapacity, is a congenital anomaly or birth defect or other important medical events. Other events that may not result in death, are not life threatening, or do not require hospitalization, may be considered an SAE when, based upon appropriate medical judgment, the event may jeopardize the patient and may require medical or surgical intervention to prevent one of the outcomes listed above. The term life-threatening in the definition of SAE refers to an event in which the participant was at risk of death at the time of the event; it does not refer to an event which hypothetically might have caused death if it were more severe.

To ensure no confusion or misunderstanding of the difference between the terms serious and severe, which are not synonymous, the following note of clarification is provided. The term severe is often used to describe the intensity (severity) of a specific event (as in mild, moderate or severe myocardial infarction). The event itself, however, may be of relatively minor medical significance (such as severe headache). This is not the same as ‘serious’, which is based on participant and/or event outcome or action criteria usually associated with events that pose a threat to a participant's life or functioning as defined in the bullet points above. Seriousness (not severity) serves as a guide for defining regulatory reporting obligations.

A serious adverse reaction (SAR) is defined as an AE (expected or unexpected) that is both serious and, in the opinion of the reporting investigator, believed with reasonable probability, to be due to one of the study treatments, based on the information provided. A suspected unexpected serious adverse reaction (SUSAR) is defined as an SAR, the nature or severity of which is not consistent with the applicable product information (such as an investigator’s brochure for an unapproved investigational product or summary of product characteristics for an approved product).

### Causality

The relationship of each AE to the trial medication must be determined by a medically qualified individual to be either related or not related. Related, for these purposes, requires the AE to follow a reasonable temporal sequence from trial medication administration. It cannot reasonably be attributed to any other cause. Not related, for these purposes, requires that the AE is probably produced by the participant’s clinical state or by other modes of therapy administered to the participant.

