#### Recording and reporting procedures for AEs and SAEs

Dexamethasone is a commonly used medication in a primary care setting; it has well defined safety profiles and is being used in this trial for authorized indications. As a result of this no non-SAEs will be recorded in this study. All SAEs occurring during the one month participants are enrolled on the trial will be recorded.

A participant may voluntarily withdraw from the trial due to what he or she perceives as an intolerable AE. AEs that result in a participant’s withdrawal from the study will be recorded on the withdrawal form. The relationship of AEs to the study medication will be assessed by a medically qualified investigator. The severity of events will be assessed on the following scale: 1 = mild, 2 = moderate or 3 = severe.

All SAEs must be reported to the PC-CTU within one working day of discovery or notification of the event. The PC-CTU will perform an initial check of the report, request any additional information and ensure it is reviewed by the Chief Investigator on a weekly basis. The PC-CTU will also ensure that it is reviewed at the next Data Monitoring Committee meeting. All SAE information must be recorded on an SAE forms and faxed to the PC-CTU. Additional information received for a case (follow-up or corrections to the original case) need to be detailed on a new SAE form and faxed to the PC-CTU.

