#### SUSAR reporting

In collaboration with the University of Oxford’s Clinical Trials Research Governance (CTRG) the Chief Investigator will report all SUSARs to the competent authorities (MHRA in the UK), the research ethics committee concerned and host NHS Trusts. Fatal or life-threatening SUSARs will be reported within seven days and all other SUSARs within 15 days. Any additional relevant information will be reported within eight days of the initial report. The Chief Investigator will also inform all investigators concerned of relevant information about SUSARs that could adversely affect the safety of participants.

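### The safety section sets three different causality standards, so one serious event can be an adverse reaction under one rule and unrelated, or unclassifiable, under another

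*Protocol article*

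**What the plan says.** Three places in the safety part of the protocol article set a causality threshold.

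- **Definitions, adverse reaction.** The threshold is low. An event qualifies if a "causal relationship between a study medication and an AE is at least a reasonable possibility - the relationship cannot be ruled out". Either the reporting professional or the Sponsor may make that judgement.
- **Definitions, SAR and SUSAR.** A SAR is a serious event that the reporting investigator believes, with reasonable probability, is due to a study treatment. A SUSAR is a SAR whose nature or severity does not match the product information.
- **Causality.** Each event "must be determined by a medically qualified individual to be either related or not related". The first condition for the positive answer is timing: "Related, for these purposes, requires the AE to follow a reasonable temporal sequence from trial medication administration". The second follows at once: "It cannot reasonably be attributed to any other cause". For the negative answer: "Not related, for these purposes, requires that the AE is probably produced by the" participant's own condition or by other treatment.

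The SUSAR reporting section gives expedited reporting (seven days if fatal or life-threatening, 15 days otherwise) to SUSARs only. No section says which of the three standards prevails.

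**The concern.** The Causality section is the instruction that the assessor works from, and it is stricter than the definition it should put into practice. It asks whether any other cause is reasonable. The adverse reaction definition asks whether the drug can be excluded. In an infected patient both can be true at once: the infection may reasonably explain the event and the steroid may still have contributed.

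This matters for the trial's own safety question. The Objectives include showing that dexamethasone does not increase hospital admission with complications of sore throat, with peritonsillar abscess as the example. Such an event can readily be put down to the presenting infection, which is the kind of explanation that the negative category accepts.

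At stake is whether an unexpected serious event is recognised as a SAR, and so as a SUSAR, in time for expedited reporting. The classification also carries more weight here because non-serious events are not recorded and no safety stopping criteria are defined.

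**Working it through.** The protocol states no figure on this point, so there is nothing to recompute. The check is to apply the three standards to the same event.

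Take a serious event with plausible timing after the dose. Suppose that any competing cause is the participant's condition or another treatment, so that the timing and source conditions of the Causality section are met. Four situations remain.

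| Situation | Adverse reaction (Definitions) | SAR wording (Definitions) | Causality section |
|---|---|---|---|
| A. No other reasonable cause | Yes | Yes on a natural reading | Related |
| B. Another cause reasonable but not probable; drug possible | Yes | Depends on how reasonable probability is read | Neither category applies |
| C. Another cause probable; drug not ruled out | Yes | Doubtful | Not related |
| D. Drug ruled out; other cause established | No | No | Not related |

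1. In A and D the three standards agree.
2. In C they conflict directly. The adverse reaction definition is met because the link cannot be excluded. The Causality section returns the negative answer because another cause is probable, and it does not ask whether the drug has been excluded.
3. In B the compulsory two-way choice has no valid answer. The event fails the positive category because another cause is reasonable. It fails the negative category because that cause is not probable. The two categories are not complements.
4. The SAR wording is a third threshold. Reasonable probability is not the same test as a possibility that cannot be excluded, nor the same as the absence of any other reasonable cause. It also rests on the reporting investigator's opinion alone, whereas the adverse reaction definition also admits the Sponsor's.
5. SUSAR status follows from SAR status, and expedited reporting follows from SUSAR status. In C, and in B if the assessor settles on the negative answer, an unexpected serious event could therefore miss expedited reporting although it meets the protocol's own definition of an adverse reaction.

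One reading had to be settled. The sentence on other causes stands between the definitions of the two categories. Its only sensible place is as the second condition for the positive category.

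**The case against.** The strongest reply is that the Causality section does not by itself decide expedited reporting. SUSAR status runs through the SAR definition, and neither that definition nor the SUSAR reporting section refers to the related label. The Sponsor's judgement could also bring a case in as an adverse reaction. This stands. It means that a missed SUSAR is possible but not shown. It also means that correcting the Causality section alone would leave the SAR threshold untouched.

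The second reply is that the safeguards are real, and this stands too. All SAEs in the month are recorded and sent to the trials unit within one working day. The Data Monitoring Committee reviews them quarterly and cumulatively, and can act between meetings. Annual safety reports go to the regulator. Admissions and attendances with complications are secondary outcomes compared by randomised arm, which needs no causality judgement. The Statistics section describes no analysis of related SAEs, so no stated analysis is biased. These safeguards limit the consequence, but quarterly or annual review does not replace seven- or 15-day reporting.

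A reader might infer three stronger things that the document does not support:

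- **That such events never reach the regulator, or are systematically misclassified.** The Sponsor route, the separate SAR wording and the annual reports all count against this. An event must also be unexpected against product information that is not shown, so whether abscess or sepsis would qualify cannot be settled here.
- **That nearly every infection complication would be called unrelated.** That depends on how assessors would judge individual cases, and the document does not tell us.
- **That the weekly review uses up the reporting window.** The trials unit is to "ensure it is reviewed by the Chief Investigator on a weekly basis", and "Fatal or life-threatening SUSARs will be reported within seven days". But the article does not say when the seven days start, or that the causality judgement waits for that review. It assigns the judgement to a medically qualified investigator.

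**Conclusion.** The point holds as an internal contradiction. Three causality standards are in force, two of them conflict outright when another cause is probable but the drug is not excluded, and the two-way choice leaves a gap when another cause is reasonable but not probable. Condensing does not explain this, because the article states all three rules.

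Its size cannot be put as a rate. The article gives no expected number of SAEs and expects those associated with a single dose to be very rare. The contradiction bears on any serious event in situations B or C. The harm is a possible missed or inconsistent SAR or SUSAR classification. It is not a loss of SAE data or a bias in a planned comparison. The link from wording to missed reporting assumes that investigators forming the SAR opinion are guided by the Causality section, which is likely but not stated.

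The correction should be made: it touches patient safety and needs only a change of wording.

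**What to change.** Use one causality standard throughout. Take the adverse reaction wording in Definitions (a reasonable possibility that cannot be ruled out) and put it in place of reasonable probability in the SAR definition and of the two conditions for a related event in the Causality section. Define not related as its exact complement, so that every event falls into one category and only one. In the same edit, say whether the Sponsor's judgement counts for a SAR as it does for an adverse reaction.

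The cost is protocol and SAE-form wording, with somewhat more events classed as related. Sample size, outcomes and the planned analyses do not change.

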#### Recording and reporting procedures for AEs and SAEs

Dexamethasone is a commonly used medication in a primary care setting; it has well defined safety profiles and is being used in this trial for authorized indications. As a result of this no non-SAEs will be recorded in this study. All SAEs occurring during the one month participants are enrolled on the trial will be recorded.

A participant may voluntarily withdraw from the trial due to what he or she perceives as an intolerable AE. AEs that result in a participant’s withdrawal from the study will be recorded on the withdrawal form. The relationship of AEs to the study medication will be assessed by a medically qualified investigator. The severity of events will be assessed on the following scale: 1 = mild, 2 = moderate or 3 = severe.

All SAEs must be reported to the PC-CTU within one working day of discovery or notification of the event. The PC-CTU will perform an initial check of the report, request any additional information and ensure it is reviewed by the Chief Investigator on a weekly basis. The PC-CTU will also ensure that it is reviewed at the next Data Monitoring Committee meeting. All SAE information must be recorded on an SAE forms and faxed to the PC-CTU. Additional information received for a case (follow-up or corrections to the original case) need to be detailed on a new SAE form and faxed to the PC-CTU.

#### Data Monitoring Committee

The appointed and independent Data Monitoring Committee (DMC) conducts a review of all SAEs for the study reported during the quarter and cumulatively. They report their findings to the Trial Steering Committee who in turn report to the Trial Management Group. The main aims of this review are as follows: to ensure the safety and rights of each patient in the trial, to pick up any trends, such as increases in expected and unexpected events, and take appropriate action, to monitor the trial data and review and analyze as outlined in the statistical analysis plan, systematically or as requested by the Trial Steering Committee, to seek additional advice or information from investigators where required, to evaluate the risk, in terms of safety and ethics, of the trial continuing and take appropriate action where necessary and to act or advise, through the Chairman or other consultant, on incidents occurring between meetings that require rapid assessment. The Data Monitoring Committee will also suggest provision of training specific groups to the Trial Steering Committee as required.

#### SUSAR reporting

In collaboration with the University of Oxford’s Clinical Trials Research Governance (CTRG) the Chief Investigator will report all SUSARs to the competent authorities (MHRA in the UK), the research ethics committee concerned and host NHS Trusts. Fatal or life-threatening SUSARs will be reported within seven days and all other SUSARs within 15 days. Any additional relevant information will be reported within eight days of the initial report. The Chief Investigator will also inform all investigators concerned of relevant information about SUSARs that could adversely affect the safety of participants.

